### Data management

Proprietary turning data will be acquired from the Leaf Patient Monitoring System. Compliance to preventative turning care will be defined by two measures. The first will sum the overall time the patient is overdue for turning care, divided by the total monitoring time, and will be reported as a percentile of time. For example, if a patient was on the unit for 4 h and did not receive preventative turning care at the second hour, but instead at the third hour (1 h overdue), then the patient’s care was in compliance for 3 of the 4 h of their length of stay. This would, therefore, represent a time in compliance of 75 %. If they received the turn on schedule, the compliance would be at 100 %. The second measure will divide a patient’s length of stay into 2 h turning blocks. In the above example, if the patient was turned once in their 4 h stay, compliance to turning would equal 50 %. Although we believe that the time in compliance is more appropriate than the proportion of turns within 2 h blocks, we will test and report on both measures as the latter reflects current clinical care practices.

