### Study endpoints

#### Primary

The following endpoints will be evaluated:Difference in compliance rates with preventative turning practices between the treatment and control groups, as continuously measured by the Leaf Patient Monitoring System during the patients’ ICU stayDifference in the proportion of HAPUs between the treatment and control groups

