#### Primary endpoint

An independent-samples Student’s *t* test will be used to evaluate for differences in preventative turning compliance between the two groups. To test for differences in pressure ulcer rates between the treatment groups, a 2 × 2 table with chi-square statistic will be used. To further evaluate for differences in pressure ulcer rates between treatment groups over time, a Kaplan-Meier survival analysis with log-rank test will be used. For all analyses, tests are deemed to be significant if significance is less than *p* <0.05. Device-related pressure ulcers from catheters or tubes are generally unrelated to turning and are not included in this analysis.

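### Two unranked primary endpoints are tested in up to four ways, each at p <0.05, although the sample size and its 5% level cover only the pressure ulcer proportion

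*Protocol article*

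**What the plan says.** All references are to the protocol article.

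- **Study endpoints, Primary.** Two endpoints stand side by side. The first is "Difference in compliance rates with preventative turning practices between the treatment and control groups"; the second is the between-group difference in the proportion of HAPUs. Neither is ranked above the other, and the section does not say whether one or both must succeed.
- **Data management.** Compliance has two definitions: the share of monitored time not overdue for a turn, and turns counted in 2 h blocks. The authors state a preference ("we believe that the time in compliance is more appropriate than the proportion of turns" in blocks) but add that "we will test and report on both measures as the latter reflects current clinical care practices".
- **Statistical analysis, Primary endpoint.** A Student's t test "will be used to evaluate for differences in preventative turning compliance between the two groups". For ulcers, a 2 × 2 "table with chi-square statistic will be used". A second ulcer test follows: "To further evaluate for differences in pressure ulcer rates between treatment groups over time, a Kaplan-Meier survival analysis with log-rank test will be used". The section then sets one threshold: "For all analyses, tests are deemed to be significant if significance is less than" 0.05.
- **Sample size calculation.** The 1812 patients (906 per group) come from a two-sided Z test of two proportions, 5% against 2.5% HAPU, with 80% power at the 5% level. Compliance does not enter.

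**The concern.** The text fixes two co-listed primaries and a flat threshold for every test. Read literally, a significant result on either endpoint is a primary success, and the 5% level used to size the trial does not describe the chance of a spurious primary finding when neither outcome differs.

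The two endpoints also differ in kind. Compliance is what the intervention acts on: the dashboard is switched on for treatment patients and off for controls. The Background cites an earlier single-center study in which compliance rose from 64 to 98% after the system was introduced. A significant compliance result is therefore likely whatever happens to ulcers. Yet the Background and the Discussion frame the question as whether optimal turning reduces HAPUs, and the Discussion faults prior studies for not assessing that outcome. As written, the trial could report a primary endpoint met without having answered that question.

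**Working it through.** **1. The plan's own figure.** Inputs from the sample size section: p1 = 0.05, p2 = 0.025, two-sided alpha 0.05, power 80%. With pooled variance under the null and p̄ = 0.0375:

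n per arm = [1.960·√(2·0.0375·0.9625) + 0.8416·√(0.05·0.95 + 0.025·0.975)]² / 0.025²

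= [1.960·0.26868 + 0.8416·0.26810]² / 0.000625 = 905.4, rounded up to 906.

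This gives 1812 in total, an exact match, and power at 906 per arm is 80.0%. The whole two-sided 5% is used by the HAPU test.

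**2. Count of tests.** Two compliance measures by t test, plus chi-square and log-rank for ulcers: four, each at 0.05.

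**3. Chance of at least one false positive if neither outcome differs.**

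- Two endpoints, one test each, assumed independent: 1 − 0.95² = 9.75%.
- For two tests of the same outcome with correlated normal statistics, P(either |Z| > 1.96) depends on the correlation. No correlation is given in the article; these are assumptions:

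| Assumed correlation | P(either significant) |
|---|---|
| 0.50 | 9.1% |
| 0.90 | 7.0% |
| 0.98 | 5.9% |

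- All four tests, with compliance independent of ulcers: 1 − (1 − a)(1 − b), where a is for the compliance pair (correlation 0.5 to 0.9) and b for the ulcer pair (0.90 to 0.98).
  - Lowest: 1 − (1 − 0.0704)(1 − 0.0593) = 12.5%.
  - Highest: 1 − (1 − 0.0907)(1 − 0.0704) = 15.5%.
- A patient-level simulation (906 per arm, assumed 5% ulcer rate in both arms, exponential stay and ulcer times, compliance correlation 0.7, 20,000 runs) agrees: about 6% for either ulcer test, 10% for one compliance test plus chi-square, and 14% for all four.

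**4. If compliance truly improves.** A significant compliance test is then a true positive, and the only null left is HAPU. Its error is 5% by chi-square alone, and 5.9% to 7.0% if either ulcer test may count (the 0.98 and 0.90 rows above).

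**5. How easily compliance reaches significance.** Power ≈ Φ(d / [SD·√(2/906)] − 1.96). The article gives no SD, so a range is assumed:

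| Gap | SD 20 | SD 30 | SD 40 |
|---|---|---|---|
| 10 points | >99.9% | >99.9% | >99.9% |
| 5 points | >99.9% | 94% | 76% |

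For scale, the earlier study's change was 98 − 64 = 34 points.

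**6. Cost of the alternatives.** Splitting alpha equally (0.025 each) lowers HAPU power at 906 per arm to Φ[(0.025·√906 − 2.2414·0.26868)/0.26810] = Φ(0.561) = 71.2%; restoring 80% would need 1097 per arm (2194 in total). A fixed order with HAPU first leaves the HAPU test at 0.05, with 80.0% power. A fixed order with compliance first makes the HAPU test depend on a gate whose power is 76% at a 5-point gap and SD 40.

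**The case against.** The strongest reply is that the inflated figures need neither outcome to differ, while the protocol expects compliance to rise. If it does rise, nothing about compliance is a false positive and the ulcer error is close to nominal. That stands, and it shifts the weight of the point from error rate to interpretation.

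Three further arguments also have force.

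- The sample size section states 5% for one test on HAPU proportions. A reader might infer that it promises a family-wise rate and breaks that promise; it does not, and the calculation is correct for the test it describes.
- A reader might also infer an open menu in which the sponsor may claim whichever ulcer test succeeds. The wording does not support that. The endpoint is a proportion, the sizing test is a Z test of proportions (equivalent to the uncorrected chi-square in a 2 × 2 table), and the log-rank test is introduced as a further evaluation. Time in compliance is likewise the stated preference. These pointers are informal, but they indicate the lead analyses.
- Nothing in the article says that compliance alone would support an ulcer-prevention claim, and rules for overall success are often left to an analysis plan, which is not shown here.

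What survives is that none of these pointers ranks compliance against HAPU, the largest single source of inflation. The article does not merely leave the matter open: it names both endpoints as primary and sets p <0.05 for every analysis. If both were required to succeed, no alpha adjustment would be needed, but the article does not say so.

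**Conclusion.** The point holds in a limited form, as a should-fix. Two unranked primary endpoints are tested in up to four ways at 0.05, while the sample size and its full 5% belong to the HAPU proportion.

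If neither outcome differs, at least one false-positive primary result has a probability of about 10% for the two endpoints (independence assumed), or about 12.5-15.5% over all four tests (correlations assumed). If compliance improves as expected, the ulcer error is 5%, or about 6-7% if either ulcer test is allowed to count. The practical risk is then that a positive primary result is declared on a process measure while HAPU is unchanged. That a compliance result is nearly assured rests on assumed SDs and on a gap of about 10 points or more.

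The sample size is not wrong. It is valid for HAPU proportion by chi-square at the full 0.05, and the article should say that this is the test on which the ulcer conclusion depends.

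**What to change.** In Study endpoints (Primary) and Statistical analysis (Primary endpoint), state:

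1. HAPU proportion, compared by chi-square, is the first primary test at two-sided 0.05.
2. Time in compliance is tested at two-sided 0.05 only if step 1 is significant; otherwise it is reported as a process measure.
3. The log-rank test and the 2 h block measure are supportive.
4. Any claim of ulcer prevention rests on step 1 alone.

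The opposite order, compliance first, is less suitable. It would leave a primary success on compliance as likely as now, and it could block the only sized clinical test if the carry-over between groups described in the Discussion narrows the compliance gap.

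The cost is a few sentences. The 906 per arm and 80% HAPU power are kept, whereas an equal alpha split would reduce power to about 71%. The small downside is that compliance loses formal confirmatory status if HAPU is not significant. The change should be made before any outcome data are compared by arm.

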#### Secondary endpoint

To test for differences in HAPUs between patients based on admitting service (medical or surgical), a Kruskal-Wallis rank test will be used. Stages of pressure ulcers (based on NPUAP staging criteria) will represent the ranks to be measured. A difference will exist if the significance level of the test statistic is *p* <0.05.

In creating explanatory models, multivariate logistic regression will be used. First, univariate testing of each variable in relationship to the endpoint (hospital-acquired pressure ulcer) will be performed. Only variables having a maximum significance with the endpoint of *p <*0.20 will be included in the multivariate model. Age and sex will be reintroduced to the models if they fail to meet the inclusion criteria and all other variables will be entered into the model in a forward stepwise fashion. This will be rerun until only significant variables remain. Three logistic regression models will be constructed: all ICU patients, only medical patients, and only surgical patients.

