### Pressure ulcer staging

The National Pressure Ulcer Advisory Panel (NPUAP) staging criteria will be used to stage all HAPUs [11]. Staging will be completed by an expert RN blinded to the patients’ study allocation. Adjudication will occur with the study team for any wounds that are difficult to stage.*Stage I, non-blanchable erythema*: intact skin with non-blanchable redness of a localized area usually over a bony prominence. Darkly pigmented skin may not have visible blanching; its color may differ from the surrounding area. The area may be painful, firm, soft, warmer or cooler as compared to adjacent tissue. Category I may be difficult to detect in individuals with dark skin tones. This stage may indicate “at risk” persons*Stage II, partial thickness skin loss*: partial-thickness loss of dermis presenting as a shallow, open ulcer with a red-pink wound bed, without slough. This may also present as an intact or open/ruptured serum-filled or sero-sanginous-filled blister. It presents as a shiny or dry, shallow ulcer without slough or bruising*. This category should not be used to describe skin tears, tape burns, incontinence-associated dermatitis, maceration or excoriation. *Bruising indicates deep tissue injury*Stage III, full-thickness skin loss*: full-thickness tissue loss. Subcutaneous fat may be visible but bone, tendon or muscle are *not* exposed. Slough may be present but does not obscure the depth of tissue loss. This *may* include undermining and tunneling. The depth of a category/stage III pressure ulcer varies by anatomical location. The bridge of the nose, ear, occiput and malleoli have no (adipose) subcutaneous tissue and category/stage III ulcers can be shallow. In contrast, areas of significant adiposity can develop extremely deep category/stage III pressure ulcers. Bone/tendon is not visible or directly palpable*Stage IV, full-thickness tissue loss*: full-thickness tissue loss with exposed bone, tendon or muscle. Slough or eschar may be present. This stage often includes undermining and tunneling. The depth of a category/stage IV pressure ulcer varies by anatomical location. The bridge of the nose, ear, occiput and malleoli have no (adipose) subcutaneous tissue and these ulcers can be shallow. Category/stage IV ulcers can extend into muscle and/or supporting structures (e.g., fascia, tendon or joint capsule) making osteomyelitis or osteitis likely to occur. Exposed bone/muscle is visible or directly palpable

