#### Secondary

Secondary measures are to:Evaluate and describe, any differences identified in hospital-acquired pressure ulcer rates and stages between medical and surgical patient groupsDevelop explanatory models of contributing clinical factors to HAPUs for the three groups: all ICU patients, medical patients only, and surgical patients only

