### Sample size calculation

Using a two-sided *Z* test of the difference between proportions with 80 % power and a 5 % significance level, a sample size of 1812 patients, 906 in each group, will be sufficient to detect a clinically important difference of 50 % between the groups in the rate of HAPUs. This assumes that a 50 % difference represents a change from a prevalence rate of 5 % for pressure ulcers in the control group, to a rate of 2.5 % for pressure ulcers in the treatment group. Conservatively, with an estimated enrollment of 200 subjects per month, study enrollment is expected to be between 7 and 10 months’ duration.

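### One stage-ranked Kruskal-Wallis test cannot answer both halves of the rates-and-stages endpoint by service, and the rank of ulcer-free patients is not stated

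*Protocol article*

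**What the plan says.** The protocol article, Study endpoints, Secondary, sets out to evaluate and describe "any differences identified in hospital-acquired pressure ulcer rates and stages between medical and surgical patient" groups. That is a two-part question: how often ulcers occur in each service, and how severe they are.

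Statistical analysis, Secondary endpoint, gives one named test for it: "To test for differences in HAPUs between patients based on admitting service (medical or surgical), a Kruskal-Wallis rank test will be used". The ranked variable is then fixed: "Stages of pressure ulcers (based on NPUAP staging criteria) will represent the ranks to be measured". The decision rule follows: "A difference will exist if the significance level of the test statistic is" below 0.05.

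Under Pressure ulcer staging, the NPUAP "staging criteria will be used to stage all HAPUs". The section describes stages I, II, III and IV, and gives no category for a patient without an ulcer.

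The chi-square and log-rank tests under Primary endpoint compare the two treatment groups, not the two services.

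**The concern.** The ranked variable is defined only for patients who have an ulcer, while half of the endpoint concerns how many patients get one. The article does not say whether ulcer-free patients are left out or ranked below stage I. This choice decides which question the test answers. Under one coding, a doubling of the ulcer rate in one service would usually give a non-significant result. Under the other, a large difference in severity would. With a single p-value as the decision rule, either result could be reported as no difference between services on the whole endpoint. If the coding is settled only after the data are seen, the question answered could also depend on the result.

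**Working it through.** **Inputs from the article (Sample size calculation).** The design is "Using a two-sided *Z* test of the difference between proportions with 80 % power and a 5 % significance level", with "a sample size of 1812 patients, 906 in each group", and HAPU rates of 5% (control) and 2.5% (treatment).

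**Reproducing the plan's figure.** With pooled variance and no continuity correction:

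n per arm = [1.960 × √(2 × 0.0375 × 0.9625) + 0.842 × √(0.05 × 0.95 + 0.025 × 0.975)]² / 0.025² ≈ 905.4, rounded up to 906, so 1812 in total with power 0.800. The stated sample size is reproduced and is not in dispute.

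**How many patients have a stage.** 906 × 0.05 + 906 × 0.025 = 45.3 + 22.65 = 67.95, or about 68 of 1812. About 1744 patients (96%) have none.

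**Why the two codings answer different questions.** If no ulcer is ranked lowest, the 1744 ulcer-free patients share the mid-rank (1 + 1744)/2 = 872.5. The 68 ulcer patients occupy ranks 1745 to 1812, with mean 1778.5. Having an ulcer moves a patient by about 906 ranks (1778.5 − 872.5). Stage can move a patient by at most 67 (1812 − 1745). Rate dominates and stage hardly counts. If only ulcer patients are ranked, the number of ulcer-free patients does not enter the statistic at all.

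**Fixed example** (assumed counts): 46/906 versus 23/906 ulcers, with stages I to IV of 14/20/8/4 and 7/10/4/2, which are the same proportions.
- Stages only: H = 0.00, p = 1.00.
- No ulcer = 0, all patients: H = 7.96, p = 0.0048.
- 2 × 2 chi-square: 7.97, p = 0.0048.

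**Simulation**, 3000 trials per row, α = 0.05, 1812 patients. The article gives no medical/surgical split, no rates by service and no stage mix, so these are assumptions. The 5% and 2.5% are borrowed from the arms. The common stage mix is 30/50/15/5%. The unequal mixes are 50/40/8/2% versus 10/40/30/20%.

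| Split | Scenario | Stages only | No ulcer = 0 | Chi-square |
|---|---|---|---|---|
| 50:50 | Rates 5% v 2.5%, same stages | 0.054 | 0.804 | 0.805 |
| 35:65 | Rates 5% v 2.5%, same stages | 0.049 | 0.781 | 0.783 |
| 50:50 | Rates 3.75% each, unequal stages | 0.996 | 0.042 | 0.042 |
| 35:65 | Rates 3.75% each, unequal stages | 0.994 | 0.056 | 0.056 |

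A separate run of 4000 trials (906 per service, 5% v 2.5%, common mix 40/40/15/5%) gave 0.054, 0.810 and 0.810, so the first row does not hang on one stage mix.

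If the service with the lower rate (2.5% v 5%) has the worse stages (50:50 split, the unequal mixes above), the stages-only test rejects in 0.989 of trials and the zero-coded test in 0.793. The first is driven by severity and the second by rate, so they would point to opposite services.

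**The case against.** The strongest reply is that the article compares patients by admitting service and nowhere excludes the ulcer-free. Ranking them lowest is a natural way to run the test, and it then matches the chi-square on rates. The coding of a no-ulcer category could be left to a fuller document. The article also plans univariate screening and logistic models of HAPU, including one for all ICU patients, in which service could be a candidate. The endpoint is worded as evaluating and describing, so rates by service would probably be shown anyway.

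Part of this stands. A reader might infer that ulcer-free patients have no rank and that the test cannot detect a rate difference. That would be reading an exclusion into silence, and it holds only if stages I to IV alone are ranked. The reply does not rescue the plan, however, because the coding that recovers the rates loses the stages. The mismatch lies between a stated endpoint and a stated test, ranked variable and threshold, so it is more than an omitted detail. The logistic models do not name service. They select variables by a p < 0.20 screen and forward stepwise entry, and two of the three are fitted within a single service.

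Three other strong readings are not supported:
- **Lesions lost from the ranking.** The Stage II note that "Bruising indicates deep tissue injury" might suggest that such lesions drop out. The same section says that all HAPUs are staged and that difficult wounds are adjudicated. All that can be said is that no rank is stated for a HAPU outside stages I to IV.
- **Confounding by treatment arm.** Randomization is stratified by admitting service, so the arms should be balanced within each service. Adjustment for arm is a refinement.
- **Zero coding as the severity test.** The third and fourth rows of the table show that it would be nearly blind to severity.

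**Conclusion.** The point holds in this form: one stage-ranked Kruskal-Wallis test is given for a two-part endpoint, the rank of about 96% of patients is not stated, and neither natural coding answers both parts. Ranked on stages alone, the test rejects at about its 5% type I error level when rates differ as 5% versus 2.5%, where a chi-square rejects in about 80% of trials. With no ulcer ranked lowest, it rejects in about 5% of trials when stage mixes differ sharply at equal rates, where the stages-only test rejects in over 99%.

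These percentages rest on the assumed split, service rates and stage mixes and are not predictions for this trial. The pattern was the same for 50:50 and 35:65 splits and follows from how the ranks are built. The defect concerns one secondary, non-randomized comparison. It is worth correcting before analysis but does not touch the primary endpoints, the sample size or the treatment conclusion.

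**What to change.** Replace the single test with two, each tied to one half of the endpoint:

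1. **Rates.** Compare HAPU yes/no between medical and surgical patients, in all patients, with a 2 × 2 chi-square or a logistic model, optionally adjusted for arm and unit.
2. **Stages.** Keep the rank test on each patient's worst stage, restricted to patients with an ulcer and labelled as a severity comparison. State the category for any HAPU that does not fit stages I to IV.

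Report both results side by side. The cost is about two sentences of wording and no new data, since ulcers are staged and service is recorded for randomization. There are two downsides. This secondary endpoint then carries two tests in place of one. The severity comparison rests on a small group (about 68 patients) selected by outcome, so it should be read descriptively.

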## Background

Pressure ulcers are insidious complications that affect approximately 2.5 million patients and account for approximately US$11 billion in annual health care spending each year [1]. Acutely ill patients are at risk for the development of pressure ulcers due to immobility, reduced perfusion, and prolonged duration of mechanical ventilation [2]. In 2008 the Centers for Medicare and Medicaid Services discontinued reimbursement for facility-acquired pressure ulcers (also known as hospital-acquired pressure ulcers, HAPUs), as these are considered an avoidable complication often described as a “never event.” Given the tremendous burden that pressure ulcers place on the individual patient and the health care system, there is a substantial need for improved prevention methods [3, 4].

Pressure ulcers form when there is sustained pressure, predominately over bony prominences such as the sacrum, heels, occiput, and shoulders. Unrelieved pressure causes compression of cellular tissue, impaired blood flow, and can lead to localized tissue damage and cellular death. Pressure ulcers initially appear as areas of reddened skin but can quickly develop into large open wounds if the pressure is not relieved.

To prevent pressure ulcers, the currently accepted standard of care is to turn patients at least every 2 h, day and night. However, there are no published research studies that support the every 2-h turning schedule in critically ill patients. Notwithstanding, studies have estimated that compliance with patient-turning protocols are around 60 % and that a significant number of patients are not being turned as frequently as recommended [5, 6]. In intensive care units (ICUs), compliance to turning protocols is even lower, ranging from 38 to 51 % [7, 8]. Potential explanations for this low compliance include low prioritization of turning, difficulty in monitoring a patient’s position, ineffective turn reminders/alerts, and sub-optimal caregiver staffing ratios – all of which hinder efforts to prevent pressure ulcers.

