**Fig. 3 Fig3:**
[figure not shown]
User-Dashboard – Leaf Patient Monitoring Interface. *Used with permission from Leaf Healthcare, Inc.

If the subject is enrolled in the control group, the unit secretary will turn the User-Dashboard “off” by selecting the “control patient” check-box in the Leaf Patient Monitoring System. This will turn the sensor information off and therefore not display any information to the User-Dashboard. Patients in the control group will continue to receive standard care practices, that is, pressure ulcer-prevention activities initiated by nurses using their usual care routines. Nursing care will not be “optimized” by the Leaf Patient Monitoring System, with the system withholding any data related to turning frequency, position schedule, and decompression time. The patient sensor will continue to collect these data for the purposes of research analysis only.

Each patient’s participation within the study begins within the first hour of arrival to a study unit and ends upon discharge or transfer from the study unit. Upon leaving the unit, the patient sensor will be removed and the patient will be discharged automatically from the Leaf Patient Monitoring System.

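### The explanatory models and the medical-versus-surgical comparison ignore time at risk, so a factor or service with longer ICU stays can appear to contribute to pressure ulcers

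*Protocol article*

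**What the plan says.** Four parts of the protocol article bear on this.

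- **Observation window.** Under Recruitment/Intervention, participation starts within the first hour on the unit and "ends upon discharge or transfer from the study unit". Each patient therefore has a different time at risk.
- **Secondary aims.** Under Study endpoints, Secondary, the trial will describe "differences identified in hospital-acquired pressure ulcer rates and stages between medical and surgical patient" groups. It will also model the clinical factors that contribute to HAPU in all ICU patients and in each service separately.
- **Secondary methods.** Under Statistical analysis, Secondary endpoint: "multivariate logistic regression will be used. First, univariate testing of each variable in relationship to the endpoint", that is, HAPU. The screen is at p<0.20 and is followed by forward stepwise entry. Only age and sex are brought back regardless of the screen. The services are compared by Kruskal-Wallis with NPUAP stages as the ranks. No patient-days, offset or time-to-event term is stated for either analysis.
- **Where time is used.** Under Statistical analysis, Primary endpoint, Kaplan-Meier curves and a log-rank test are planned "To further evaluate for differences in pressure ulcer rates between treatment groups over time". They are planned for the randomized arms only.

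**The concern.** A patient who stays longer has more days on which an ulcer can form. Between the randomized arms this matters less, because randomization balances expected stay at entry. It does not do so between medical and surgical patients, or between patients with and without a clinical factor. Those are the comparisons that the article analyses without time at risk.

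The stated aim is to explain which clinical factors contribute to ulcers, not only to predict who leaves the unit with one. In a per-stay analysis, two quite different situations look alike: a factor that raises the daily risk, and a factor that leaves daily risk unchanged but goes with a longer stay. A reader would be led to different conclusions about prevention in the two cases. The same holds if one service simply keeps its patients longer.

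**Working it through.** **The plan's own figure.** Inputs from Sample size calculation: 5% versus 2.5%, two-sided 5% level, 80% power.

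n per group = [1.96·√(2·0.0375·0.9625) + 0.8416·√(0.05·0.95 + 0.025·0.975)]² / 0.025² = (0.5266 + 0.2256)² / 0.000625 ≈ 905.4, so 906 per group and 1812 in total. The stated size is reproduced and is not in dispute. Expected patients with HAPU: 906·0.05 + 906·0.025 ≈ 68.

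**Assumptions for the illustration.** The article gives no lengths of stay and no shape for the daily risk, so these are assumed:
- overall HAPU risk 3.75%, the midpoint of the two planning rates;
- a factor present in half of 1812 patients (906 versus 906);
- the factor multiplies mean stay by r and does not change daily risk;
- constant daily risk λ and exponential stays with mean m in the reference group.

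**Odds ratio.** P(HAPU) = λm/(1 + λm), so the odds are λm. With mean stay r·m the odds are λrm. The odds ratio is therefore r, whatever m is.

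**Size.** λm is set so that the average of the two risks is 3.75%. The chance of a significant result, in the direction of the longer stay, comes from the two-proportion Z test at 906 versus 906.

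| r | risk, shorter stay | risk, longer stay | odds ratio | p<0.05 | passes p<0.20 |
|---|---|---|---|---|---|
| 1.25 | 3.35% | 4.15% | 1.25 | 14% | 35% |
| 1.5 | 3.03% | 4.47% | 1.5 | 37% | 63% |
| 2 | 2.54% | 4.96% | 2.0 | 77% | 92% |

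Worked line for r = 2:
- odds 0.0254/0.9746 = 0.0261 and 0.0496/0.9504 = 0.0522, ratio 2.0;
- pooled standard error √(2·0.0375·0.9625/906) = 0.00893, unpooled 0.00891;
- z = (0.0242 − 1.96·0.00893)/0.00891 ≈ 0.75, so power is about 77%.

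**Simulation check.** Repeated runs of 1000 to 4000 trials gave p<0.05 in 14–15%, 31–38% and 77–78% at r = 1.25, 1.5 and 2, and in about 5% when stays were equal. The excess therefore comes from exposure. Events per patient-day gave rate ratios of 1.00 to 1.02 and rejected in about 4–6%.

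**The service comparison.** About 96% of patients have no ulcer, so a rank test on stage is driven by who has any ulcer. With an assumed stage mix that is the same in both services, Kruskal-Wallis rejected in about 14%, 32–39% and 78–79% of simulated trials at the three ratios, and in about 6% with equal stays.

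**Sensitivity to when the risk falls.** Suppose all risk lies in the first 4 days and the reference mean stay is 4 days (assumed). Expected days at risk are m·(1 − e^(−4/m)): 2.53 for m = 4, 2.92 for m = 6 and 3.15 for m = 8. The exposure ratios are 2.92/2.53 = 1.15 and 3.15/2.53 = 1.25. At this low overall risk the odds ratios are close to those values: about 1.15 at 1.5 times the stay and about 1.25, instead of 2.0, at twice the stay. A daily risk that rises during the stay would push the figures up.

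**The case against.** The best defence is that risk per stay is a legitimate quantity. The primary ulcer endpoint is itself a proportion of patients. If a factor doubles the stay and so roughly doubles the chance of an ulcer on the unit, an odds ratio near 2 correctly describes risk per stay. The secondary aims do not say whether risk per stay or risk per day is meant. This stands, and it is why the logistic model should be kept beside a time-at-risk model and not simply removed. It does not settle the matter, because the aim is explanatory and the per-stay model alone cannot separate the two routes.

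Three stronger readings are tempting, and the article does not support them.

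- A reader might infer that anything which lengthens the stay will be reported as a cause. At 1.25 times the stay the chance of p<0.05 is only about 14%. The figures are for one factor alone and not for its survival through the stepwise model. The article also speaks of contributing factors, not causes.
- A reader might infer that the services are compared on a yes/no ulcer score. They are compared on ranked stages. The exposure problem carries over, as the simulation shows, but the method must be described correctly.
- A reader might infer that whole-stay totals, and so consequences of ulcers, will enter the models. The Background does name "prolonged duration of mechanical ventilation" as a risk factor, but only as background. The candidate variables are not listed, and an article may leave that list to the analysis plan. No fault can be charged on that ground.

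Nor is the main point a detail left for later. The article fixes the model type, the screen, the entry rule, the three populations and the service test.

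**Conclusion.** The point holds in this limited form. Both secondary analyses take no account of time at risk in comparisons that randomization does not protect, so a difference in length of stay can pass for a difference in ulcer risk. Under constant daily risk the odds ratio equals the ratio of mean stays. Modest differences in stay give a modest chance of a misleading result, and a doubling makes one likely. If risk falls mainly early in the stay, the distortion is much smaller. The true size cannot be known from the article, since the stay ratios, hazard shape and factor prevalence are all assumed. The randomized comparison of ulcer proportions and the sample size are not affected. The change is worth making because it alters what the explanatory aim can conclude and costs little.

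**What to change.** In Statistical analysis, Secondary endpoint:

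- Fit the explanatory models as cause-specific Cox regression of time from ICU admission to first HAPU, with patients leaving the risk set at ICU exit or death. Poisson regression with log patient-days to first HAPU or ICU exit as offset is an alternative.
- Use covariates known at ICU admission.
- Keep the per-stay logistic model beside it, labelled as description.
- For medical versus surgical patients, report HAPUs per 1000 patient-days at risk, with a rate ratio and 95% confidence interval, beside the proportion and the stage comparison.
- Do not rely on total length of stay as an adjustment covariate, because it includes time after the ulcer appeared.

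The cost is a little more analysis work. Ulcer time and ICU exit time are already needed for the planned Kaplan-Meier analysis, and no extra patients are required. One consequence should be stated in the report: a factor that acts only through a longer stay will show in the per-stay model but not in the time-at-risk model.
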